#### Temporary suspension of a treatment session

The study-gas treatment session will be immediately suspended if any of the following occurs:Methemoglobin (MetHb) will be measured 15 min after initiation of each treatment session and at the end of treatment. If MetHb exceeds 7%, the current inhaled NO treatment will be stopped.The inhaled NO_2_ concentration exceeds the prespecified threshold of 3 ppm.A device, respiratory circuit, gas-delivery, or monitoring-system malfunction occurs and cannot be immediately corrected.Clinically significant active bleeding, marked hemodynamic instability, bronchospasm, or unexplained deterioration in oxygenation potentially related to the study gas occurs, as judged by the treating physician.

#### Permanent discontinuation of study-gas treatment

Study-gas treatment administered for research purposes will be permanently discontinued if any of the following occurs:Completion of the planned 5-day treatment course.Antimicrobial susceptibility results do not confirm MDR bacterial infection.Withdrawal of informed consent.MetHb ≥7% or inhaled NO_2_ ≥3 ppm on two occasions.A suspected serious adverse reaction related to the study gas.The treating physician or principal investigator judges that continued intervention poses an unacceptable risk.

Participants who discontinue the intervention will continue scheduled follow-up and will be included in the intention-to-treat analysis.

#### Trial sponsor, study intervention supply

The trial sponsor is Jiangdu People’s Hospital Affiliated to Yangzhou University. The sponsor is responsible for overall trial oversight, regulatory and ethics submissions, maintenance of essential trial documentation, and ensuring that the trial is conducted in accordance with the approved protocol and applicable regulations.

This investigator-initiated trial is funded by the Yangzhou City Basic Research Program (Joint Special Project), Health and Wellness Category (2025-3-45). The funder has no role in the design of the study; collection, management, analysis, or interpretation of data; decision to submit the results for publication; or preparation of the manuscript.

Both the intervention and control groups will receive study-gas treatment using the NOwill N300 Nitric Oxide Generation and Delivery System (Noling Biotechnology Co., Ltd., Nanjing, China). The equipment will be provided by the hospital, and the manufacturer will provide software support only. The manufacturer will not participate in protocol development, participant recruitment, clinical care, randomization, data collection, outcome assessment, statistical analysis, interpretation of results, or publication decisions, and will not have access to unblinded individual-level data.

#### Sample size

As no previous studies have reported the effect of high-dose inhaled NO on CPIS outcomes in patients with severe pneumonia caused by MDR bacteria, the sample size was estimated using preliminary retrospective data from our center. These data included four patients who received high-dose inhaled NO and 11 patients who received standard treatment. The between-group difference in CPIS was 3 points, with a standard deviation of 4 points. Assuming a two-sided α of 0.05 and a β of 0.20 (80% power), at least 28 participants per group are required, for a total of 56 participants. Allowing a 10% dropout rate, the target sample size is 64 participants with confirmed MDR bacterial infection (32 per group). Assuming that 65% of patients with suspected MDR infection will have confirmed MDR bacterial infection, approximately 98 patients with suspected MDR infection will need to be enrolled.

#### Outcomes

##### Primary outcome

The primary outcome is the change in CPIS from baseline to day 7.

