##### Analysis of populations

Three analysis populations will be defined: the modified intention-to-treat population with confirmed MDR pathogens (mITT-MDR), the per-protocol population with confirmed MDR pathogens (PP-MDR), and the safety population [24].

The safety population will include all randomized participants who receive at least one administration of study gas (NO or sham gas). Participants will be analyzed according to the treatment actually received, regardless of whether MDR bacterial infection is subsequently confirmed by antimicrobial susceptibility testing. Safety outcomes will be analyzed in the safety population.

The mITT-MDR population will include all participants who have at least one pathogen isolated from a baseline lower respiratory tract specimen that meets the prespecified MDR definition on antimicrobial susceptibility testing. Participants will be analyzed according to their randomized treatment assignment. The primary and secondary outcomes will be analyzed in the mITT-MDR population.

The PP-MDR population will include participants in the mITT-MDR population who complete at least 80% of the prespecified study-gas treatment sessions, have no major protocol deviations that could affect efficacy assessment, and complete assessment of the primary outcome. The PP-MDR analysis will be conducted only as a sensitivity analysis of the mITT-MDR analysis.

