##### Data collection and management

Baseline data, underlying diseases, comorbidities, and the Acute Physiology and Chronic Health Evaluation II score on day 1 will be collected. Daily vital signs, Sequential Organ Failure Assessment score, and mechanical ventilation parameters will be monitored. Blood gas results will be collected before treatment, during the first 7 days, and at discharge. For patients receiving invasive mechanical ventilation at enrolment or on day 7, lower respiratory tract aspirates (endotracheal aspirates, ETAs) will be collected *via* the endotracheal tube using aseptic techniques. For patients who have been extubated by day 7 and can expectorate effectively, spontaneously expectorated deep sputum specimens will be collected. Blood samples collected on days 1 and 7 will be used to measure citrullinated histone H3 by enzyme-linked immunosorbent assay and cell-free DNA concentration.

Primary and secondary outcomes will be evaluated by independent assessors blinded to treatment allocation using standardized case report forms. To ensure data security, all source data will be anonymized using unique study IDs and stored on a password-protected server. Missing data will be minimized through standardized follow-up procedures. The amount, timing, and reasons for missing data will be summarized by randomized group.

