##### Subgroup and sensitivity analyses

Prespecified subgroup analyses of the primary outcome will be conducted according to the presence or absence of septic shock, pneumonia type (community-acquired pneumonia [CAP] versus hospital-acquired pneumonia [HAP]), and concomitant use of inhaled antibiotics.

A sensitivity analysis of the primary outcome will be performed in the PP-MDR.

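### The day-7 primary comparison has no place for participants who die before day 7, and the only named sensitivity analysis cannot show whether that matters

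*Protocol article*

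**What the plan says.** - **Endpoint** (Primary outcome): "The primary outcome is the change in CPIS from baseline to day 7". Nothing there, or elsewhere in the article, assigns a score or rank to a participant who dies earlier.
- **Test** (Statistical analysis): the change is compared by independent-samples t test if normally distributed, otherwise by Wilcoxon rank-sum.
- **Analysis sets** (Analysis of populations): mITT-MDR takes everyone with a confirmed baseline MDR pathogen, as randomized, and carries the primary outcome. PP-MDR is the subset with at least 80% of sessions and no major deviation who also "complete assessment of the primary outcome".
- **Sensitivity analysis** (Subgroup and sensitivity analyses): "A sensitivity analysis of the primary outcome will be performed in the PP-MDR". No other is named.
- **Missing data** (Data collection and management): "The amount, timing, and reasons for missing data will be summarized by randomized group". No handling rule follows.
- **Sample size**: "The between-group difference in CPIS was 3 points, with a standard deviation of 4 points". From this, "Assuming a two-sided α of 0.05 and a β of 0.20 (80% power), at least 28 participants per group are required". The inflation sentence reads "Allowing a 10% dropout rate, the target sample size is 64 participants with confirmed MDR bacterial infection (32 per group"; it does not say whether deaths count as dropout.
- **Setting**: invasive ventilation is an entry criterion (Participants), and the Abstract and Introduction describe mortality as high. No rate is given, at day 7 or later.

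**The concern.** A t test or rank-sum test needs a value for each participant. Someone who dies on day 4 has no day-7 CPIS and, without a rule, is not in the comparison. Survival to day 7 happens after randomization and may itself be changed by the gas. Comparing only those scored at day 7 is then no longer a comparison of the randomized groups. If NO keeps more of the sickest patients alive, they are scored and pull the NO mean down, hiding benefit. If NO causes early deaths, the sickest leave the NO arm and the gas is flattered.

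A sensitivity analysis exists to probe this kind of weakness. The one chosen removes the same patients by definition, and also removes those who did not complete enough sessions, which early deaths will often not have done. Agreement between mITT-MDR and PP-MDR would therefore say nothing about early deaths.

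A smaller matter is that the loss allowance behind the 80% power does not say whether it covers deaths.

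**Working it through.** **1. The plan's own figure.** Inputs from Sample size: difference 3, SD 4, two-sided α 0.05, power 80%.

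n per arm = 2 × (1.96 + 0.8416)² × 4² / 3² = 2 × 7.849 × 16 / 9 = 27.9, so 28. Then 28 / 0.9 = 31.1, so 32 per arm and 64 in total. Both figures reproduce. Normal-approximation power at 28 per arm is 80.1%. The exact t calculation gives 78.7% at 28 and needs 29 per arm, a trivial difference.

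**2. What the 80% depends on.** 32 − 28 = 4 per arm may be lost (4/32 = 12.5%), for any reason. Exact t power, with loss unrelated to CPIS:

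| Total loss by day 7, deaths included | Scored per arm | Power |
|---|---|---|
| 10% | 32 × 0.9 = 28.8 | 79.9% |
| 20% | 32 × 0.8 = 25.6 | 74.9% |
| 30% | 32 × 0.7 = 22.4 | 68.9% |

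If deaths come on top of the 10% dropout, 32 × 0.9 × (1 − deaths), rounded down, leaves 25, 23 and 20 per arm at 10%, 20% and 30% deaths. Power is then 75.5%, 72.0% and 66.0% by the normal approximation (73.8%, 70.1% and 63.7% by exact t).

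**3. Bias among those scored at day 7.** The documents give no day-7 mortality, so the rates here are assumed. Model: latent CPIS change is normal with SD 4 in each arm. The log-odds of death rise by 1 for each SD of worse change within the arm, with the intercept set to give the stated mortality. With 2 million simulated values per arm, removing deaths improves the survivors' mean by about 0.36 points at 10% mortality, 0.69 at 20% and 1.01 at 30%. The apparent benefit of NO is the true benefit minus (control shift − NO shift):

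| True benefit | Deaths, control / NO | Apparent benefit |
|---|---|---|
| 3 | 20% / 10% | 3 − (0.69 − 0.36) = 2.67, about 2.7 |
| 3 | 30% / 10% | 3 − (1.01 − 0.36) = 2.35, about 2.4 |
| 0 | 10% / 20% | 0 − (0.36 − 0.69) = 0.33, about 0.3 in favour of NO |
| any | equal | no bias |

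**4. Does PP-MDR detect this?** Its definition requires the completed primary assessment. Every participant missing from the mITT-MDR test for want of a day-7 score is also missing from PP-MDR, so it cannot.

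**5. Price of an analysis that keeps deaths in.** 4,000 simulated trials of 32 per arm, true benefit 3, SD 4, comparing a rank-sum test with deaths ranked last against a t test in survivors:

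| Deaths, control / NO | Death unrelated to CPIS: worst-rank vs survivors | Death related as in step 3: worst-rank vs survivors |
|---|---|---|
| 20% / 20% | about 43% vs 75% | about 48% vs 80% |
| 30% / 15% | about 79% vs 73% | about 73% vs 62% |

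**The case against.** **The article never says the main analysis is limited to survivors.** mITT-MDR has no requirement to be alive or assessed at day 7, and those who stop treatment stay in follow-up and in the intention-to-treat analysis. A reader might infer that every primary analysis is by definition restricted to survivors. The text supports that only for PP-MDR. For mITT-MDR it follows from naming tests that need a value while giving deaths none. A rule could sit in the statistical analysis plan, which Data Availability mentions and which is not shown. This limits the point but does not remove it. The article itself fixes the sets, the tests, the missing-data text and the sensitivity analysis, and choosing a completers-only set as the sole check is a stated decision.

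**Deaths are not hidden.** A reader might also infer that early deaths vanish unnoticed. They do not: reasons for missing data are summarized by arm, and ICU, in-hospital and 28-day mortality are secondary outcomes in the same population. Those tables show an imbalance but do not repair the primary comparison.

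**The effects are modest.** This is fair. The spurious 0.3 points is small against an SD of 4, and the false-positive rate under no effect with 10% vs 20% deaths rises only to about 6.6%. The power figures in step 2 also treat loss as unrelated to CPIS. With equal, CPIS-related deaths of 20% and 30%, survivors-only power is about 79% and 75%.

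**Worst-rank analysis is one choice among several and can cost much power.** This is also fair, and it is why the analysis belongs in a supporting role.

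**Conclusion.** The point holds in limited form. As written, the primary test compares participants who have a day-7 CPIS, in a population whose mortality the article calls high, and the only named sensitivity analysis cannot reveal the resulting bias. On assumed mortality differing by 10 to 20 percentage points between arms, and a moderate link between CPIS course and death, a 3-point benefit shrinks by about 0.3 to 0.6 points. Excess deaths on NO of 10 points flatter it by about 0.3. If mortality is equal in the two arms, this model gives no bias. The sizes rest on assumed rates; the direction, bias against the arm with fewer deaths, holds whenever patients doing worse are likelier to die.

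It would be wrong to conclude that the sample size is miscalculated. The 28 and 32 per arm are right for their inputs, and no shortfall in power can be asserted without a day-7 mortality. What is open is whether the 10% covers deaths.

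**What to change.** 1. **Subgroup and sensitivity analyses:** add a prespecified analysis in the full mITT-MDR population. Deaths before day 7 rank below all survivors, other missing day-7 scores are imputed from baseline and day-3 CPIS (already scheduled), and arms are compared by rank-sum test. Keep PP-MDR in its present supporting role.
2. **Statistical analysis:** describe the planned test as a comparison among participants assessed at day 7, and report day-7 deaths by arm beside it.
3. **Sample size:** state that 80% power assumes about 10% total loss including deaths, with about 75% at 20% and 69% at 30% if loss is unrelated to CPIS. The 28 and 32 stay.

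The cost is wording and a little programming, with no new data. It should be settled before unblinding, because a death rule chosen afterwards carries little weight. The drawback is power: at 20% deaths in both arms the worst-rank analysis has roughly 43–48%, against 75–80% for the survivors-only test. It should therefore be a sensitivity analysis and not a condition for claiming benefit.

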##### Secondary outcomes

 In-hospital mortality, ICU mortality, and 28-day mortality.Ventilator-free days, vasopressor-free days, antibiotic-free days, ICU-free days, and hospital-free days through day 28.CPIS and Sequential Organ Failure Assessment (SOFA) scores on days 3 and 7.Microbiological eradication rate on day 7.Concentrations of citrullinated histone H3 and cell-free DNA.Daily ratio of arterial oxygen partial pressure to fractional inspired oxygen (PaO_2_/FiO_2_) from days 1 to 7.

##### Safety outcomes

Incidence of MetHb levels ≥5%, ≥7%, and ≥10%.Incidence of inhaled nitrogen dioxide (NO_2_) concentrations ≥3 ppm.Serum creatinine levels from days 1 to 7.Airway hyperreactivity events.Incidence of acute kidney injury (AKI), including stages 1, 2, and 3, during hospitalization.

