### Participants

Eligible patients must meet all the following criteria:Age 18 years or older.Diagnosis of severe pneumonia within 24 h before enrolment.Requirement for invasive mechanical ventilation.Suspected or confirmed infection caused by multidrug-resistant (MDR) bacteria; confirmation may be based on sputum or bronchoalveolar lavage fluid (BALF) culture.Written informed consent provided by the patient or a legally authorized representative.

Informed by previous studies by Di Fenza et al. [18] and Kalashnikova et al. [8], patients will be excluded if they meet any of the following criteria:Current participation in another clinical trial;Active pulmonary malignancy or a history of lung transplantation or pulmonary resection;Severe burns involving >40% of the total body surface area;Severe hepatic or renal dysfunction, defined as Child–Pugh class C hepatic impairment or an estimated glomerular filtration rate <30 mL/min;Current receipt of renal replacement therapy;Previous inhaled NO therapy before enrolment;Patients with methemoglobinemia;Major bleeding at screening.

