#### Definition of major bleeding

1. Fatal bleeding, 2. Symptomatic bleeding in a critical area or organ, such as intracranial, intraspinal, intraocular, retroperitoneal, intra-articular or pericardial, or intramuscular with compart-ment syndrome,3. Bleeding causing a fall in hemoglobin level of 20 g/L) or more, or leading to transfusion of two or more units of whole blood or red cells [23].

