#### Emergency unblinding criteria

Emergency unblinding will be permitted only for a life-threatening medical event or an event that may result in irreversible harm, when the investigator determines that knowledge of the study gas received by the participant is necessary for immediate resuscitation or subsequent critical treatment decisions.

Individual emergency unblinding may be considered if any of the following occurs:Uncontrolled respiratory or hemodynamic deterioration, including persistent hypoxemia, urgent escalation of respiratory support, circulatory shock, severe arrhythmia, or cardiac arrest, when knowledge of whether the participant received inhaled NO would alter immediate clinical management.A suspected serious adverse reaction or serious unexpected medical event related to study gas, for which treatment allocation remains necessary to guide further management after discontinuation of the study gas and standard clinical treatment.Any other emergency that is life-threatening or may result in irreversible harm, when the investigator determines that failure to unblind would compromise participant safety.

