##### Safety monitoring

During inhaled NO administration, NO2 will be continuously monitored and maintained below 3 ppm. MetHb levels will be measured 15 min after the initiation of each inhaled NO treatment session and at the end of each session. Renal function will be assessed daily using blood testing. An independent Data and Safety Monitoring Board (DSMB), comprising two external clinicians and one biostatistician, will review safety data every 6 months. No formal interim analysis of efficacy or futility and no sample-size re-estimation are planned. Serious adverse events will be reported within 24 h. The final database will be locked upon completion of the 30-day follow-up and resolution of all queries. Participant recruitment and study-gas treatment will be temporarily suspended, and an ad hoc safety review by the Data and Safety Monitoring Board (DSMB) will be initiated, if any of the following occurs:Any unexpected death assessed as at least possibly related to study-gas treatment.Two or more unexpected serious adverse events assessed as at least possibly related to study-gas treatment.In the NO group, permanent discontinuation of study-gas treatment due to methemoglobin (MetHb) ≥7% or persistent inhaled NO_2_ concentrations >3 ppm in ≥10% of participants.A clinically important and unexpected imbalance between groups in the incidence of serious adverse events, severe hypoxemia, or hemodynamic instability.A major breach of blinding, major protocol deviation, or data-integrity issue that may jeopardize participant safety or seriously compromise trial validity.

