## Discussion

High-dose NO has anti-infective and oxygenation-improving effects. Several studies have suggested that inhaled NO can reduce viral load in patients with coronavirus disease 2019 and prevent postoperative pulmonary bacterial infection [3,8,10,11]. However, the effect of high-dose NO in Severe pneumonia infection has rarely been reported. This study focuses specifically on patients with severe pneumonia associated with MDR bacteria and will evaluate whether high-dose inhaled NO improves bacterial clearance, clinical outcomes, and mortality without increasing adverse reactions.

Mechanistically, high-dose NO may exert antibacterial activity by damaging bacterial DNA, proteins, and lipid structures [3], inhibiting biofilm formation by Pseudomonas aeruginosa and Klebsiella pneumoniae [16], and enhancing immune-cell phagocytosis of resistant bacteria [25]. A pathway involving neutrophil chemotaxis, activation, neutrophil extracellular trap release, and bacterial killing has also been proposed as a potential mechanism through which high-dose NO improves outcomes in severe pneumonia [16].

High-dose inhaled NO has been recommended for severe pneumonia in a Chinese expert consensus, primarily based on evidence from severe viral pneumonia [26]. Evidence for severe bacterial pneumonia remains limited. This study selects patients with MDR infection because these patients lack safe and effective treatment options, and conventional antibiotic therapy is often less effective or requires costly advanced antibiotics. If high-dose inhaled NO improves outcomes in patients with severe pneumonia associated with MDR bacteria, it may have important implications for antimicrobial resistance and patient prognosis.

This study also includes exploratory mechanistic assessments. Neutrophil number and percentage, citrullinated histone H3, and cell-free DNA concentration in plasma can reflect neutrophil extracellular trap activity and may provide preliminary clinical evidence for the proposed mechanism of action [27,28].

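### The safety outcomes omit bleeding, haemodynamic instability and unexplained oxygenation loss, which the protocol's own suspension rule ties to the study gas

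*Protocol article*

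**What the plan says.** All places are in the protocol article.

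- *Temporary suspension of a treatment session* stops the gas if "Clinically significant active bleeding, marked hemodynamic instability, bronchospasm, or unexplained deterioration in oxygenation potentially related to the study gas occurs". Separate items cover MetHb, NO2 and equipment faults.
- *Participants* excludes "Major bleeding at screening". *Definition of major bleeding* sets out three categories, among them "Symptomatic bleeding in a critical area or organ".
- *Emergency unblinding criteria* begins with "Uncontrolled respiratory or hemodynamic deterioration, including persistent hypoxemia".
- *Safety monitoring* calls for an ad hoc DSMB review on "A clinically important and unexpected imbalance between groups in the incidence of serious adverse events, severe hypoxemia, or hemodynamic instability", and states that "Serious adverse events will be reported within 24 h".
- *Safety outcomes* has five items: MetHb thresholds, an NO2 threshold, serum creatinine, "Airway hyperreactivity events" and AKI. The Abstract, Table 1 and *Statistical analysis* carry the same five.
- *Analysis of populations* puts safety outcomes in everyone given study gas at least once, and primary and secondary outcomes in mITT-MDR.
- *Discussion* says that the trial will evaluate whether NO improves outcomes "without increasing adverse reactions".

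**The concern.** The suspension rule and the safety outcomes do not match. The suspension rule names four clinical events as possible effects of the gas. The safety list, which is the same in four places, carries a counterpart for only one of them.

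Of the five listed outcomes, MetHb and NO2 mainly reflect exposure to NO, and the sham arm receives none. Creatinine and AKI are renal. Only airway hyperreactivity describes how patients tolerate the gas clinically. If the stated list is followed, an excess of bleeding, hypotension or desaturation during NO sessions would enter no safety comparison between the arms. Any count chosen after the data are seen would be post hoc.

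**Working it through.** **1. Named hazards against stated outcomes**

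| Hazard | Where the protocol treats it as one | Safety outcome | Other between-arm comparison |
|---|---|---|---|
| Bleeding | Exclusion, full definition, suspension rule | None | None |
| Haemodynamic instability | Suspension rule, unblinding criteria, DSMB trigger | None | Vasopressor-free days, SOFA (mITT-MDR only) |
| Oxygenation loss | Suspension rule, unblinding criteria, DSMB trigger | None | Daily PaO2/FiO2 (mITT-MDR only) |
| Bronchospasm | Suspension rule | Airway hyperreactivity | None needed |
| MetHb, NO2 | Suspension, discontinuation, DSMB trigger | Threshold incidence | None needed |

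Three of the four clinical suspension reasons have no safety outcome. For two of these, the substitutes are not tied to a session: as outcomes, SOFA is taken on days 3 and 7 and PaO2/FiO2 once a day, so a fall confined to a 30-minute session can be missed.

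**2. The plan's own sample size**

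Inputs from *Sample size*: difference 3, SD 4, two-sided α 0.05, power 80%, dropout 10%, MDR confirmation 65%.

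- n per arm = 2 × (1.960 + 0.842)² × 4² / 3² = 27.9, so 28, as stated. (A t-based calculation gives 28.9; the difference does not matter here.)
- With dropout: 28 / 0.90 = 31.1, so 32 per arm and 64 in total, as stated.
- Enrolled: 64 / 0.65 = 98.5, against about 98 stated.

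The figures reproduce and are not in dispute.

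**3. Who the secondary outcomes leave out**

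98 − 64 = 34, and 34 / 98 = 35%. If all 98 receive at least one session, about a third of those exposed to study gas are in the safety population but outside mITT-MDR.

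**4. What the added outcomes could show**

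With 1:1 allocation, 98 / 2 = 49 per arm (approximate, since randomization is simple).

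- Zero events in 49: one-sided 95% upper limit = 1 − 0.05^(1/49) = 5.9% (rule of three: 3/49 = 6.1%).
- The protocol gives no event rates, so the rates below are assumptions. The half-width of a 95% interval for a risk difference is 1.96 × √(2p(1 − p)/49), with both arms at rate p.

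| Assumed rate p | Half-width (percentage points) | Power to detect a doubling of p |
|---|---|---|
| 5% | 8.6 | 15% |
| 10% | 11.9 | 28% |
| 20% | 15.8 | 58% |

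**The case against.** The best defence is that these events are not ignored. *Data collection and management* plans daily vital signs, SOFA and ventilation parameters, and blood gases before treatment and over the first 7 days. SAEs must be reported promptly, and serious bleeding would ordinarily be expected to reach that route, although the article prints no SAE definition. The DSMB reviews safety data every 6 months and is not confined to the listed outcomes. Adverse-event tables and reasons for stopping are commonly left to a full protocol or SAP, and neither is shown. The Introduction names only MetHb and kidney-injury markers as safety measures, and the list covers both.

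Much of this stands, and it rules out several stronger readings that a reader might reach:

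- *The DSMB trigger cannot be computed, or nothing collects the events.* The raw data are planned. What the article lacks is an event definition and a stated comparison.
- *The trial cannot support its safety aim.* Partial coverage exists, and the *Discussion* speaks of evaluating whether adverse reactions increase, not of showing that they do not.
- *The protocol screens for all three harms.* At entry it screens only for bleeding.
- *About 490 NO sessions would go unreported.* 49 × 10 sessions is a maximum, because gas stops when MDR infection is not confirmed, and the article does not say that suspensions go uncounted.

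The defence does not remove the mismatch. The safety list is stated and fixed in four places, so the point concerns what the list contains, not detail left to another document. Raw data and SAE reports do not amount to a prespecified comparison, and a non-serious bleed that halts a session has no place in any stated one.

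A practical objection is that the staff who run the sessions are barred from data collection. Its force is limited: the suspension rule leaves the clinical judgement to the treating physician, who is blinded according to *Randomization and blinding*. The limitations paragraph of the *Discussion* says that medical staff are not blinded, and the two must be reconciled.

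**Conclusion.** The point holds as a mismatch between the safety outcomes and the protocol's own hazards. Bleeding has no outcome, no comparison and no named DSMB trigger. Haemodynamic instability and oxygenation loss have only indirect secondary measures, in a population that leaves out about 35% of those enrolled. As written, a conclusion on adverse reactions would rest on a narrower list than the reasons for which the protocol stops the gas.

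The 35% rests on the protocol's 65% confirmation rate, on all 98 being enrolled on suspicion, and on all receiving at least one session. If some are already confirmed at entry, the share is smaller.

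The primary analysis and sample size are unaffected. This is a cheap improvement that should be made, not a flaw that invalidates the trial.

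**What to change.** Add the following to *Safety outcomes*, Table 1 and *Statistical analysis*, in the safety population, by arm, each with a risk difference and confidence interval:

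1. Major bleeding, by the definition already in the protocol.
2. Participants with a session suspension or permanent discontinuation, by the reasons already listed. This also catches bleeding that stops a session without meeting the major-bleeding definition.
3. SAE incidence, and the severe hypoxaemia and haemodynamic instability events named in the DSMB trigger. *Safety monitoring* does not define these two, so the sponsor must fix definitions before unblinding.

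The cost is a few case report form fields, completed by blinded clinical or data staff, and some protocol wording. MetHb and NO2 are already safety outcomes, so a route for those readings must already be needed. The intervals will be wide, and the report should say that they estimate harm and do not prove its absence. No stop rule, dose or sample size changes.
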